# Protocol for a prospective, multicenter, randomized, controlled trial comparing pulsed field ablation vs. cryoballoon ablation in patients with persistent atrial fibrillation (PEACE trial)

**DOI:** 10.1016/j.ijcha.2025.101819

**Published:** 2025-10-07

**Keywords:** Atrial fibrillation, Catheter ablation, Pulsed-field ablation, Cryoballoon ablation, Randomized controlled trial

## Abstract

**Background:**

Catheter ablation has become a standard treatment for atrial fibrillation (AF). However, evidence regarding the efficacy and safety of pulsed field ablation (PFA) in patients with persistent AF (PeAF) remains limited. The PEACE trial aims to evaluate the efficacy and safety of PFA compared to cryoballoon ablation (CBA) in PeAF.

**Methods:**

This prospective, multicenter, open-label, randomized controlled, non-inferiority trial (NCT07064616, UMIN000057896) will enroll 300 patients with PeAF, randomly assigned (1:1) to undergo either PFA using the PulseSelect™ or cryoballoon ablation (CBA) using the Arctic Front Advance™. The primary efficacy endpoint is atrial tachyarrhythmia recurrence within 12 months. The primary safety endpoint is procedure-related complications within 30 days. Secondary outcomes include early recurrence, changes in LA diameter, natriuretic peptide levels, and patient-reported symptoms.

**Expected results:**

We hypothesize that PFA will be non-inferior to CBA in terms of efficacy and safety.

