### Study design

2.1

The PEACE trial is a prospective, multicenter, open-label, randomized controlled non-inferiority trial conducted at three hospitals in Japan. Patients will be randomly assigned in a 1:1 ratio to undergo either PFA or CBA (Fig. 1). The study aims to enroll 300 patients (150 in each group). Stratified randomization will be conducted using a random number table, based on age (<70 or ≥70 years), sex, and left atrial (LA) diameter (<40 mm or ≥40 mm), to ensure balanced allocation across these variables. Only one investigator ([name]), who will not be involved in assigning the actual interventions, will have access to the randomization sequence. The planned enrolment period is from 18 June 2025 (the IRB-approved start date) to 31 December 2027.

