### Study endpoints

2.5

✔ Primary efficacy endpoint.•Freedom from any atrial arrhythmia (AF, atrial flutter, or atrial tachycardia) recurrence lasting ≥ 30 s after a 90-day blanking period for 12 months post-ablation✔ Primary safety endpoint.•Incidence of procedure-related complications within 30 days post-procedure✔ Secondary endpoints:•Changes in LA diameter•Changes in BNP/NT-proBNP levels•Early arrhythmia recurrence (within the 90-day blanking period)•Patient-reported symptoms assessed using the NRS scale

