### Sample size calculation

2.6

The sample size of 300 patients (150 per group) was calculated based on an assumed 12-month success rate of 54.8 % for CBA vs. 55.1 % for PulseSelect™ for PeAF as reported in previous studies [7,9]. The calculation assumed a significance level (α) of 0.05, statistical power of 80 %, and a non-inferiority margin of 1.4. For safety endpoints, a complication rate of 4.9 % was estimated for both groups. To account for potential dropouts and missing data, approximately 10 % more patients were added, resulting in 150 patients per group.

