### Statistical analysis

2.7

Time-to-event analyses will be conducted using Kaplan-Meier survival curves and compared using the log-rank test. Categorical variables will be compared using the Chi-square test or Fisher’s exact test, while continuous variables will be analyzed using the Student’s *t*-test or the Wilcoxon rank-sum test, as appropriate. A two-sided p-value of <0.05 will be considered statistically significant.

Analyses will be conducted using all available data. Missing primary outcome data will be treated as censored observations in the time-to-event analysis rather than excluded. No imputation is planned. For secondary outcomes, available-case analysis will be performed, incorporating all observed data to minimize data loss. Sensitivity analyses may be considered if the extent of missing data is substantial.

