## Discussion

3

The PEACE trial is the first randomized controlled trial to evaluate PFA using the PulseSelect™ in comparison with CBA using the Arctic Front Advance™ for patients with PeAF. The trial aims to provide critical evidence on whether PFA can achieve comparable efficacy to CBA while offering a reduced risk of complications.

Pulsed-field ablation was introduced into clinical practice in 2019. Its most distinctive feature is the tissue-selectivity of the pulsed-field energy [8]. PV stenosis is one of the serious complications associated with thermal energy-based catheter ablation procedures [11]. As of 2025, no cases of PV stenosis have been reported with PFA [12]. Furthermore, collateral damage such as esophageal ulcers, gastric hypomotility, and permanent phrenic nerve injury has not been observed. Although these complications have decreased even with the use of CBA, fatal events have still been reported. On the other hand, complications specific to PFA, such as hemolysis, hemolysis-related renal dysfunction [13], and coronary spasm [14], have been reported. This study will specifically assess these complications in comparison with those associated with thermal energy-based ablation systems. In this study, we will assess the incidence of hemolysis and related renal insufficiency via laboratory parameters (hemoglobin, creatine kinase, serum creatinine, and urinary hemoglobin) at baseline, day 1, 6, and 12 months. Moreover, the long-term efficacy of the PFA system remains insufficiently established, particularly in patients with PeAF. While thermal ablation typically produces an irreversible lesion, electroporation induced by pulsed-field energy has been reported to be partially reversible [15]. It remains challenging to determine whether the pulsed-field applications reliably create irreversible lesions, as local potential often disappears temporarily, regardless of the reversibility of the electroporation. Therefore, the durability of the created lesion following PFA will be a critical outcome of interest. A retrospective study comparing the recurrence of AF after three different energy sources for PeAF demonstrated [16] that penta-spline PFA and Arctic Front Advance™ cryoablation achieved compatible outcomes, outperforming radiofrequency catheter ablation.

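### Safety non-inferiority is hypothesised without a safety margin or power, and a non-significant test of difference on about 7 events per arm cannot support it

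*Protocol article*

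**What the plan says.** - **Hypothesis** (Abstract, Expected results): "We hypothesize that PFA will be non-inferior to CBA in terms of efficacy and safety".
- **Endpoint** (section 2.5): the primary safety endpoint is "Incidence of procedure-related complications within 30 days post-procedure".
- **Sample size** (sections 2.1 and 2.6): 300 patients, 150 per group. The calculation rests on an "assumed 12-month success rate of 54.8 % for CBA vs. 55.1 % for PulseSelect™ for PeAF", with α 0.05, 80% power and one margin of 1.4, for which neither scale nor endpoint is named. On safety there is one sentence: "For safety endpoints, a complication rate of 4.9 % was estimated for both groups". It is followed by an allowance of about 10% for dropout.
- **Analysis** (section 2.7): "Categorical variables will be compared using the Chi-square test or" Fisher's test, at a two-sided 0.05 level. No confidence limit is compared with a margin.
- **Discussion**: the trial is meant to show "whether PFA can achieve comparable efficacy to CBA while offering a reduced risk of complications".

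**The concern.** A non-inferiority hypothesis is defined by its margin. Here the hypothesis covers two endpoints, but nothing identifies a margin for safety. The complication rate stands in the sample-size section as if safety had been sized, although no power is given for it. The only analysis described for a binary endpoint tests for a difference, and failure to reject a null of no difference is not evidence of non-inferiority when events are few. The Discussion then words the safety aim as a reduction in risk, which is a different hypothesis from the one in the abstract.

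At stake is what the trial may say about complications. The Discussion names haemolysis, related renal dysfunction and coronary spasm as harms specific to PFA that this trial will assess. A safety conclusion drawn from a test that usually misses a doubling of complications would not be sound.

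**Working it through.** **1. What drives the 150 per group.** The article does not give its formula. Read 1.4 as a risk-ratio margin for recurrence, with recurrence of 1 − 0.551 = 0.449 (PFA) and 1 − 0.548 = 0.452 (CBA), one-sided α 0.05 and 80% power:

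n = (z₀.₉₅ + z₀.₈₀)² × [pT(1 − pT) + R²·pC(1 − pC)] / (pT − R·pC)²

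= 6.183 × [0.449×0.551 + 1.96×0.452×0.548] / (0.449 − 0.6328)²

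= 6.183 × 0.7329 / 0.03378 = 134.1, so 135 per arm, and 135/0.9 = 150.

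The stated size is reproduced without using the 4.9%.

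**2. Expected events.** 150 × 0.049 = 7.35 per arm (6.6 if 135 are evaluable).

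**3. Precision of the difference.** SE = √(2 × 0.049 × 0.951 / 150) = 0.0249, so the 95% half-width is 1.96 × 0.0249 = 0.0489, or 4.9 points. This is as large as the assumed rate itself. With 135 per arm it is 5.1 points. As an example, 7 against 7 events in 150 per arm gives a 95% interval of about −5.2 to +5.2 points for the difference and about 0.36 to 2.78 for the risk ratio.

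**4. Margins with 80% power if both rates are 4.9%.** Smallest absolute margin = (z₁₋α + z₀.₈₀) × SE.
- One-sided 0.05: (1.645 + 0.842) × 0.0249 = 6.2 points, so an upper limit of 4.9 + 6.2 = 11.1%.
- One-sided 0.025: (1.960 + 0.842) × 0.0249 = 7.0 points, so an upper limit of 11.9%.
- With 135 per arm: 6.5 and 7.4 points.

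For smaller margins at 150 per arm, power at one-sided 0.05 / 0.025 is 33% / 22% (3 points), 48% / 36% (4 points) and 64% / 52% (5 points).

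**5. The tests actually described, under a true doubling.** The 9.8% rate is an illustration, not a figure from the protocol. Exact enumeration over both binomials, 150 per arm, 4.9% against 9.8%, two-sided 0.05:
- Chi-square without correction: power 36%, non-significant about 64% of the time.
- Fisher: power 29%, non-significant about 71% of the time.

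Average expected events would be 150 × (0.049 + 0.098)/2 = 11 per arm, so chi-square would normally be chosen and 64% is the more relevant figure. An observed 7 against 16 events still gives Fisher p = 0.08.

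**The case against.** The other side has several fair points.

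- **The claim is one abstract sentence.** The Introduction speaks of comparing efficacy and safety, and section 2.5 lists the safety endpoint as an incidence. No success rule in the body includes safety. This makes it partly a wording problem, but the sentence is the trial's stated hypothesis and concerns an endpoint labelled primary.
- **The full protocol or SAP may hold a margin.** It may. But the article does report a margin, α, power and a safety rate, and these do not support the hypothesis it states. The limits on precision follow from the published rate and size, so no further document can remove them.
- **The power figures assume equal rates.** This stands. If PFA were at 3% against 4.9% (assumed rates), power for a 5-point margin would be 87% (one-sided 0.025) or 92% (one-sided 0.05).
- **The Discussion sentence is prose about the aim, not an analysis hypothesis.** Agreed. It needs aligning, but it does not commit the trial to a superiority test.

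A reader might also infer more than the text supports:
- **That 1.4 is the safety margin.** The margin follows the efficacy rates, precedes the safety sentence and reproduces the sample size on efficacy. Power figures from applying it to 4.9% describe a design that the article does not state.
- **That the protocol will treat p > 0.05 as proof of safety.** It never says so, and section 2.7 does not name the safety endpoint. A test of difference is simply the only binary analysis described.
- **That the trial can establish nothing about safety.** Wide margins are powered. Whether 6 to 7 points is acceptable is a clinical judgement that the article does not make.

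**Conclusion.** The point holds in this form: non-inferiority in safety is hypothesised, but the article gives no safety margin, no power and no analysis that could establish it, and the Discussion words the aim differently. At 150 per arm and 4.9% in both arms, the expected 95% half-width is about 4.9 points, and 80% power is reached only for margins of about 6.2 to 7.0 points. A non-significant chi-square or Fisher result therefore cannot carry the safety claim.

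The precision and margin figures rest on equal rates of 4.9%, 150 evaluable patients per arm and the normal approximation. The finding that safety played no part in the sample size rests on reading 1.4 as a recurrence risk ratio at one-sided 0.05, which yields the stated size.

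**What to change.** Preferred change:
- Remove safety from the non-inferiority hypothesis in the abstract.
- In section 2.6, keep the 4.9% but label it as the assumption behind the expected precision, not as a basis for the sample size.
- In section 2.7, report the PFA minus CBA difference in 30-day complications with a 95% score-type confidence interval, and give the expected half-width (about ±5 points).
- State that no claim of non-inferiority or reduced risk will rest on a non-significant p-value.

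Equally valid alternative: keep the claim, but with a clinically justified safety margin on a named scale, a decision rule that compares a confidence limit with it, and the actual power at 150 per arm.

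Whichever is chosen, align the Discussion sentence on reduced risk with it. The cost is a weaker safety claim and probably a protocol amendment, since enrolment was planned from 18 June 2025. With enrolment planned to 31 December 2027, the change can be made before outcome data are compared. No additional patients are needed for the preferred change. The alternative might need more: at 4.9% in both arms, a 5-point margin takes 231 per arm (one-sided 0.05) or 293 (one-sided 0.025) before dropout.

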**Conclusions:**

The PEACE trial will provide essential data regarding the efficacy and safety of PFA compared to CBA in patients with PeAF, potentially informing future clinical practice.

## Introduction

1

Atrial fibrillation (AF) is the most common sustained tachy-arrhythmia worldwide and is associated with increased morbidity and mortality [1]. Catheter ablation has been established as an effective rhythm control strategy and is currently the first-line treatment for paroxysmal AF [[1], [2], [3]]. However, complications and recurrences remain concerns. Since the early 2000 s, radiofrequency (RF) ablation has been the dominant energy source. Cryoballoon ablation (CBA), introduced in 2014, enables standardized pulmonary vein isolation (PVI) with reduced operator-dependent variables [4,5]. The high durability of PVI using CBA was demonstrated [5,6], and CBA has been approved for use in patients with persistent AF (PeAF) [7].

More recently, pulsed field ablation (PFA) has emerged as a non-thermal, tissue-selective modality minimizing collateral damage [8]. However, data remain limited, particularly in PeAF. The PulseSelect™ PFA system (Medtronic, Minneapolis, MN, USA), an over-the-wire, circular PFA catheter, was introduced in 2024 [9] and is currently approved for PeAF. However, data on its efficacy and safety in PeAF remain scarce. Therefore, the PEACE (PulsEd field Ablation versus Cryoballoon ablation in patients with pErsistent atrial fibrillation) aims to compare the clinical efficacy and procedural safety of PFA (PulseSelect™) and CBA in patients with PeAF.

## Methods

2

### Study design

2.1

The PEACE trial is a prospective, multicenter, open-label, randomized controlled non-inferiority trial conducted at three hospitals in Japan. Patients will be randomly assigned in a 1:1 ratio to undergo either PFA or CBA (Fig. 1). The study aims to enroll 300 patients (150 in each group). Stratified randomization will be conducted using a random number table, based on age (<70 or ≥70 years), sex, and left atrial (LA) diameter (<40 mm or ≥40 mm), to ensure balanced allocation across these variables. Only one investigator ([name]), who will not be involved in assigning the actual interventions, will have access to the randomization sequence. The planned enrolment period is from 18 June 2025 (the IRB-approved start date) to 31 December 2027.

**Fig. 1 f0005:**
[figure not shown]
Study design and randomization process of the PEACE trial. All patients will be randomly assigned in a 1:1 ratio to either the PFA or the CBA group.

### Study population

2.2

#### Inclusion criteria

2.2.1

* Age between 18 and 85 years.* Diagnosed with PeAF (lasting less than one year or requiring cardioversion).* Eligible for catheter ablation according to current Japanese guidelines [2,10].* Able to provide written informed consent.

#### Exclusion Criteria

2.2.2

* Diagnosis of Paroxysmal or long-standing persistent AF (defined as duration > 1 year).* History of prior catheter ablation or surgical ablation for AF.* Left atrial diameter > 55 mm.* Known contraindications to contrast agents (e.g., bronchial asthma, renal impairment, or contrast allergy).* Considered unsuitable participation by the investigators.

### Ablation procedures

2.3

All patients will undergo a standard pre-procedural evaluation. Continuation or discontinuation of antiarrhythmic drugs prior to enrollment will be at the discretion of the treating physicians. Anti-arrhythmic drugs will be discontinued for at least five half-lives of each drug before the index CA. Ablation procedures will be performed using CE-marked PFA or CBA systems as part of routine clinical care. All ablation procedures will be performed under general anesthesia, using propofol, dexmedetomidine, fentanyl, and a neuromuscular blocker. Respiratory support will be provided via a laryngeal mask airway (igel®, Intersurgical Ltd., Wokingham, Berkshire, UK) with mechanical ventilation. Following a single *trans*-septal puncture using 8.5Fr SL-0 sheath (Abbott, St Paul, MN, USA), substrate mapping will be created using a high-density mapping catheter (HD-Grid®, Abbott, St. Paul, MN, or Octaray®, Biosense Webster, Diamond Bar, CA) with three-dimensional mapping system (EnSite X®, Abbott, St. Paul, MN, or CARTO 3®, Biosense Webster, Diamond Bar, CA) to enhance catheter localization and minimize fluoroscopic time. Before the Pulsed-field or cryo application, atropine is administered unless contraindicated.

The PulseSelect™ PFA system (Medtronic, Minneapolis, MN) will be used exclusively in the PFA group. Following pre-mapping, the SL-0 sheath will be exchanged for a 10Fr FlexCath Contour™ (Medtronic, Minneapolis, MN), after which the PulseSelect™ catheter will be introduced. Pulsed field energy will be delivered in four trains per application as the standard setting. The total number of PFA applications will be at the discretion of operators.

The Arctic Front Advance™ cryoballoon (Medtronic, Minneapolis, MN) will be used exclusively in the CBA group for this study. Similarly, after pre-mapping, SL-0 sheath will be exchanged for 12Fr FlexCath Contour™. Once the cryoballoon is inserted, cryo-application will be delivered to each PV. Application time will be set to 180–240 s per pulmonary vein, or 120 s after confirmation of PV isolation. An esophageal temperature monitoring catheter (Esophaster®, Japan Lifeline, Tokyo, Japan) will be inserted in all CBA group patients to minimize the risk of esophageal injury. If the temperature falls below 15 °C, the cryo-application will be immediately terminated.

After the treatment, post-mapping will be performed using a high-density mapping catheter to confirm the PVI and delineate the lesion area.

If atrial flutter, atrial tachycardia, or immediate recurrence of AF (IRAF) will occur or be induced during the procedure, additional ablation can be performed at the operator’s discretion. Any additional prophylactic ablation will not be allowed. All such events and treatments will be documented for subsequent analysis.

All procedures will be performed by the physicians who have at least 50 AF ablation cases annually and also have experience using PulseSelect™ and Arctic Front Advance™ Cryoballoon system in at least 10 cases before this study. All participating centers performed more than 150 AF ablations per year.

### Follow-up data collection

2.4

Complications will be assessed as safety outcomes. Incidence of cardiac tamponade, transient/permanent phrenic nerve palsy, esophageal injury, and stroke events will be documented. Coronary spasm events will be documented during the procedure; if suspected, coronary angiography will be performed and vasodilator therapy administered. Groin hematoma or other bleeding complications after the procedure will also be assessed within 30 days after the index procedure. These events will be recorded as predefined safety endpoints to ensure consistent adjudication across participating centers.

Patient-reported symptom burden will be assessed using the Numeric Rating Scale (NRS: range 0–10) on the day following the index ablation. Since hemolysis and hemolysis-related renal insufficiency were reported in patients treated with PFA, laboratory parameters, including hemoglobin, creatinine kinase, serum creatinine, and urinary hemoglobin, will be measured at baseline, post-procedure day 1, at 6 and 12 months. Echocardiography and Holter monitoring will also be performed at 6 and 12 months. Seven-day Holter ECG monitoring is mandatory at each time point to evaluate the recurrence. Standard 12-lead ECGs, 24-hour or 7-day Holter ECG monitoring can also be performed at the physician’s discretion on other patient visits. Arrhythmia recurrence is defined as any atrial arrhythmia lasting ≥ 30 s, occurring after a 90-day blanking period, and detected by either 12-lead or Holter monitoring.

### Study endpoints

2.5

✔ Primary efficacy endpoint.•Freedom from any atrial arrhythmia (AF, atrial flutter, or atrial tachycardia) recurrence lasting ≥ 30 s after a 90-day blanking period for 12 months post-ablation✔ Primary safety endpoint.•Incidence of procedure-related complications within 30 days post-procedure✔ Secondary endpoints:•Changes in LA diameter•Changes in BNP/NT-proBNP levels•Early arrhythmia recurrence (within the 90-day blanking period)•Patient-reported symptoms assessed using the NRS scale

### Sample size calculation

2.6

The sample size of 300 patients (150 per group) was calculated based on an assumed 12-month success rate of 54.8 % for CBA vs. 55.1 % for PulseSelect™ for PeAF as reported in previous studies [7,9]. The calculation assumed a significance level (α) of 0.05, statistical power of 80 %, and a non-inferiority margin of 1.4. For safety endpoints, a complication rate of 4.9 % was estimated for both groups. To account for potential dropouts and missing data, approximately 10 % more patients were added, resulting in 150 patients per group.

### Statistical analysis

2.7

Time-to-event analyses will be conducted using Kaplan-Meier survival curves and compared using the log-rank test. Categorical variables will be compared using the Chi-square test or Fisher’s exact test, while continuous variables will be analyzed using the Student’s *t*-test or the Wilcoxon rank-sum test, as appropriate. A two-sided p-value of <0.05 will be considered statistically significant.

Analyses will be conducted using all available data. Missing primary outcome data will be treated as censored observations in the time-to-event analysis rather than excluded. No imputation is planned. For secondary outcomes, available-case analysis will be performed, incorporating all observed data to minimize data loss. Sensitivity analyses may be considered if the extent of missing data is substantial.

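### Section 2.7 states only a test for a difference and never applies the 1.4 margin, so the stated rule does not test the non-inferiority hypothesis

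*Protocol article*

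**What the plan says.** The objective is stated in the abstract, "We hypothesize that PFA will be non-inferior to CBA in terms of efficacy and safety", and in section 2.1: "The PEACE trial is a prospective, multicenter, open-label, randomized controlled non-inferiority trial conducted at three hospitals in Japan". The primary efficacy endpoint in section 2.5 is freedom from atrial arrhythmia, defined by "recurrence lasting ≥ 30 s after a 90-day blanking period for 12 months post-ablation".

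Section 2.6 sizes the trial on an "assumed 12-month success rate of 54.8 % for CBA vs. 55.1 % for PulseSelect™ for PeAF" and adds: "The calculation assumed a significance level (α) of 0.05, statistical power of 80 %, and a non-inferiority margin of 1.4". It gives neither the scale of 1.4 nor the sidedness of alpha.

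Section 2.7 gives the analysis: "Time-to-event analyses will be conducted using Kaplan-Meier survival curves and compared using the log-rank test". Its only decision threshold is "A two-sided p-value of <0.05 will be considered statistically significant". Its missing-data paragraph says that patients without the primary outcome are censored in the time-to-event analysis, which ties the primary outcome to this log-rank route. Section 2.7 mentions no margin, effect estimate, confidence limit or shifted null hypothesis.

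**The concern.** Sections 2.6 and 2.7 address different hypotheses. A non-inferiority test has to reject the hypothesis that pulsed field ablation (PFA) is worse than cryoballoon ablation (CBA) by the margin or more. The log-rank test named in 2.7 has equality of the two curves as its null. If it does not reject, nothing has been learned about the margin.

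Two things are at stake. If the two devices perform as the sponsor expects, the stated rule will almost always end without an answer to the primary question. And a non-significant p-value leaves room for an informal conclusion of non-inferiority, whose error rate the plan does not control and which becomes easier to reach as events are lost.

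**Working it through.** **Inputs.** From section 2.6: success 54.8% (CBA) and 55.1% (PFA), so recurrence qc = 0.452 and qt = 0.449; margin 1.4; alpha 0.05; power 80%; about 10% added for dropout; 150 per arm. From section 2.7: log-rank test, two-sided 0.05. Assumptions: the scale of 1.4 is unstated, so each reading is tried; hazard ratio (HR) figures assume proportional hazards; evaluable patients range from 135 to 150 per arm.

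**1. Reproducing the sample size.** Non-inferiority on the recurrence risk ratio, linear form, one-sided 0.05:

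n = [qt(1−qt) + 1.4²·qc(1−qc)]·(1.645 + 0.842)² / (1.4·qc − qt)²

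- Variance term: 0.2474 + 1.96 × 0.2477 = 0.7329.
- Distance to the margin: 0.6328 − 0.449 = 0.1838.
- n = 0.7329 × 6.183 / 0.03378 = 134.1, so 135 per arm; 135/0.9 = 150. This matches the plan.

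Other readings do not match:

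| Reading of the margin | Per arm after dropout |
|---|---|
| Risk ratio 1.4, one-sided 0.025 (171 evaluable) | 190 |
| Hazard ratio 1.4, one-sided 0.05 | 256-270 |
| Odds ratio 1.4 | about 458 or more |

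The trial therefore appears to have been sized for a one-sided 0.05 risk-ratio test that section 2.7 does not contain.

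**2. The stated rule at the planning rates.** HR = ln(0.551)/ln(0.548) = 0.991. With 150 per arm, expected events are 150 × (0.452 + 0.449) = 135. The mean of Z is about 0.05 in size, so P(p ≥ 0.05) is about 0.95.

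**3. Chance of a non-significant log-rank test with PFA exactly at the margin.** Mean Z = √(D/4)·ln(HR), where D is the number of events.

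| Reading | PFA recurrence | HR | D at 150 / 135 per arm | Mean Z | P(p ≥ 0.05) |
|---|---|---|---|---|---|
| Risk ratio 1.4 | 63.3% | 1.67 | 162.7 / 146.4 | 3.25 / 3.09 | 9.8% / 13.0% |
| Hazard ratio 1.4 | 1 − 0.548^1.4 = 56.9% | 1.40 | 153.2 / 137.9 | 2.08 / 1.98 | 45.1% / 49.4% |

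**4. The two rules side by side.** With about 135 events, an observed HR up to exp(1.96 × 2/√135) ≈ 1.40 is still non-significant. An upper 95% limit below 1.4 needs an observed HR below 1.4/1.40 ≈ 1.00; an upper 90% limit needs one below about 1.05.

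**5. Power once the margin is used.** Risk ratio: Φ(0.1838/√(0.7329/n) − z). Hazard ratio: Φ(√(D/4)·(ln 1.4 − ln 0.991) − z), with D about 122 (135 per arm) or 135 (150 per arm).

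| Rule | 135 per arm | 150 per arm |
|---|---|---|
| Risk ratio, upper limit of 90% interval (one-sided 0.05) | 80.2% | 83.8% |
| Risk ratio, upper limit of 95% interval (one-sided 0.025) | 70.4% | 74.8% |
| Hazard ratio, upper limit of 95% interval | 47.8% | 51.9% |

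**The case against.** The strongest reply is that the article condenses a fuller plan that is not shown, and that its log-rank sentence is general and not labelled as the primary analysis. That would answer a complaint about missing detail. It does not answer this one. The article names a test and a threshold, and its censoring sentence routes the primary outcome through them. What it states does not match its own objective and sample size. It would be too strong, though, to infer that no non-inferiority analysis is planned anywhere.

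Three other strong readings go beyond the text:

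- A reader might infer that the sponsor will take p>0.05 as success. No section says so; 2.7 defines only statistical significance. The error rates in step 3 are conditional on that reading.
- A reader might say that no log-rank result could ever show non-inferiority. A result significantly favouring PFA would do so on the hazard ratio scale, because the upper 95% limit would lie below 1 and hence below 1.4. At the planning rates such a result is unlikely.
- A reader might lead with the 45-49% figure. The sample size does not fit a hazard ratio margin. The reading that fits it gives 10-13%, which should carry more weight while the scale is unstated.

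**Conclusion.** The point holds: for primary efficacy, section 2.7 states a test for a difference, the margin of 1.4 plays no part in it, and the trial's hypothesis is left untested by the stated rule. This is an error in a stated rule and should be corrected before outcomes are known.

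At the planning rates the rule is inconclusive about 95% of the time. Should non-significance be read as non-inferiority, the false-positive chance at the margin is about two to five times the nominal 2.5-5% on the risk ratio reading (9.8%/5% ≈ 2; 13.0%/2.5% ≈ 5), and higher on a hazard ratio reading. These sizes rest on the planning rates, proportional hazards and 135-150 evaluable patients per arm. The mismatch itself rests on none of them.

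**What to change.** In section 2.7:

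1. State the scale of the 1.4 margin and the one-sided alpha, consistently with 2.6. The sample size fits the ratio of 12-month recurrence at one-sided 0.05.
2. Estimate the PFA-versus-CBA effect on that scale, for example as the ratio of 12-month recurrence from the Kaplan-Meier estimates.
3. Declare non-inferiority only if the upper confidence limit is below 1.4.
4. Keep the log-rank test for superiority, once non-inferiority has been shown.
5. State the power of the chosen rule.

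The change is one of wording, but the choice of level has a price. A 90% interval on the risk ratio keeps the planned 80% at 135 evaluable per arm. A 95% interval, which corresponds to the two-sided 0.05 in 2.7, gives about 70% (75% at 150). Section 2.6 would then have to restate its power or raise enrolment to 190 per arm (171/0.9). A hazard ratio margin with a 95% interval gives only about 48-52%.
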